#### Blinding

2.9.3

The study cannot be blinded because participation in a prehabilitation program cannot be hidden from neither patients nor practitioners.

### Sample size

2.10

The sample size calculation was done using G∗Power 3.1.9.4 software using the reduction of 90 days postoperative complication rates as the primary outcome. Based on the assumption that the percentage of patients developing postoperative complications after gastrectomy is approximately 50% for the control group (based on our centers historical experience and results from RCTs)^[2,3]^ and can be reduced to 25% in the prehabilitation group (based on results of recent RCT showing 50% reduction of postoperative complications by prehabilitation),^[15]^ a group sample size of 58 patients is needed to achieve 80% power in detecting this difference in 90-days postoperative morbidity at a two-sided level of significance of 5%. Under the assumption of a drop-out rate of up to 10%, a total of 128 patients (64 per group) needs to be enrolled in the study.

### Statistical analysis

2.11

All clinical data will be analyzed on an intention to treat basis but will also be described on ‘as treated’ basis. Initially, all the clinical data will be analyzed using descriptive statistic methods. The primary outcome analysis will be based on a Chi-Square test. For secondary endpoint analysis, Chi-Square or Fisher Exact test, T-Test or Mann-Whitney test will be used where appropriate. Other statistical methods will be used if there will be a need.

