#### Sequence generation

2.9.1

Participants will be randomly assigned to either control or experimental group with a 1:1 allocation as per a computer-generated randomization schedule stratified by neoadjuvant treatment using random permuted blocks of 4 and 6. The randomization sequence was created using an online available free tool (https://www.sealedenvelope.com/).

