#### Concealment mechanism and implementation

2.9.2

The researcher assistant will prepare sequentially numbered, opaque, sealed envelopes containing randomization sheets. To distinguish patients receiving perioperative chemotherapy, the envelopes will be additionally marked. The randomization sheet will report the randomization code and assigned treatment (standard of care or prehabilitation). The prepared and sealed envelopes will be split into equal piles and delivered to the dedicated place in both study centers. At the time of randomization, the investigator (surgeon consulting the patient) will choose an envelope with the lowest number and will write the name and date of birth of the participant before opening to prevent subversion of the allocation sequence. After opening, the randomization information will be given to the patient, the baseline condition of the patient will be assessed and the case report form (CRF) will be filled in.

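### Randomisation is stratified by neoadjuvant treatment but the primary Chi-Square test is not: valid and adequately powered, yet conservative and less efficient if morbidity differs by stratum

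*Protocol article*

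**What the plan says.** Section 2.9.1 (Sequence generation) describes a "computer-generated randomization schedule stratified by neoadjuvant treatment using random permuted blocks of 4 and 6". Neoadjuvant treatment is the only stratification factor named there. Section 2.9.2 adds a logistic step for the two hospitals: "The prepared and sealed envelopes will be split into equal piles and delivered to the dedicated place in both study centers".

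On the analysis, section 2.11 says: "The primary outcome analysis will be based on a Chi-Square test". It adds only a general allowance for other methods should they be needed.

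Section 2.10 (Sample size) sizes the trial as a plain comparison of two proportions. Morbidity is taken as "approximately 50% for the control group" and it "can be reduced to 25% in the prehabilitation group", so that "a group sample size of 58 patients is needed to achieve 80% power" at a two-sided 5% level. Enrolment is set at 128 to allow for up to 10% drop-out.

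**The concern.** Blocked randomisation within strata forces the arms to be nearly equal on neoadjuvant treatment, so differences in morbidity between the strata hardly contribute to the variability of the arm comparison. The ordinary Chi-Square variance still counts that between-stratum part. If the factor predicts morbidity, the test therefore uses too large a standard error.

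The article makes a prognostic role plausible. The Introduction says that preoperative chemotherapy impairs fitness and that poor physical condition predicts complications, and the designers chose this factor to stratify on. It does not say how strong the relation is.

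At stake is efficiency and the match between design and analysis. There is a smaller point as well: the trial is open-label, and the general allowance for other methods leaves the choice between an adjusted and an unadjusted result unsettled.

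**Working it through.** **1. The plan's own figure.** Inputs from section 2.10: 50% versus 25%, two-sided 5%, 80% power. The average rate is 0.375.

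n per group = [1.960·√(2·0.375·0.625) + 0.842·√(0.50·0.50 + 0.25·0.75)]² / 0.25²
= (1.342 + 0.557)² / 0.0625 ≈ 57.7, so 58.

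Power at 58 = Φ[(0.25·√58 − 1.342) / 0.661] = Φ(0.85) = 80.2%.

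The stated 58 is reproduced, and it is the number for the unstratified test without continuity correction.

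**2. Why the variance is too large (no treatment effect, overall morbidity 50%).** Assume two equal strata with morbidity p₁ and p₂.
- The Chi-Square uses 0.50·0.50 = 0.25 per patient.
- Under balance within strata, the true figure is the mean of p₁(1−p₁) and p₂(1−p₂).
- With 58 per group, the standard error that the test uses is √(0.25·2/58) = 0.0928.
- The large-sample type I error is 2·[1 − Φ(1.960/√ratio)], where ratio is the true variance over 0.25.

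| Morbidity by stratum | Stratum odds ratio | True variance | Ratio | True SD | Large-sample type I error |
|---|---|---|---|---|---|
| 50%/50% | 1 | 0.2500 | 1.00 | 0.0928 | 5.0% |
| 40%/60% | 2.25 | 0.2400 | 0.96 | 0.0910 | 4.5% |
| 35%/65% | 3.45 | 0.2275 | 0.91 | 0.0886 | 4.0% |
| 30%/70% | 5.44 | 0.2100 | 0.84 | 0.0851 | 3.2% |

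The error runs in one direction only: the test is conservative.

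**3. Power, by simulation.** Setting: 200,000 simulated trials, 116 evaluable patients, two equal strata, allocation balanced within strata, and a common odds ratio set so that overall rates stay at 50% and 25%. CMH is without continuity correction.

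| Control morbidity by stratum | Chi-Square | CMH | Power forgone | Chi-Square type I error |
|---|---|---|---|---|
| 50%/50% | 79.9% | 80.0% | 0.1 point | 5.1% |
| 40%/60% | 80.4% | 81.6% | 1.2 points | 4.7% |
| 35%/65% | 80.9% | 83.6% | 2.7 points | 4.1% |
| 30%/70% | 81.5% | 86.0% | 4.5 points | 3.3% |

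(The 5.1% in the first row is the exact size of the test at 58 per group.)

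**4. Sensitivity to the setup.**
- With permuted blocks of 4 and 6, 10,000 trials per scenario and a 50% neoadjuvant share, the gain from CMH is 0.2 points at a stratum odds ratio of 1.5, 0.8 at 2, 1.8 at 3 and 3.6 at 5. A 30% share gives much the same: 0.2, 0.7, 1.7 and 3.7 points.
- With the blocks and the 10% drop-out both simulated (20,000 trials), power is 80.9% versus 81.7%, 81.2% versus 83.3% and 82.2% versus 85.9% in the three scenarios with a clear stratum difference. At 45%/55% there is no gain (80.7% versus 80.5%).
- At exactly 64 per group the Chi-Square has a type I error of about 4.5% with no stratum effect at all, because the data are discrete. A shortfall computed at 128 patients therefore cannot all be put down to ignoring the stratum, which is why the table uses 116.

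**The case against.** The strongest reply is that an unadjusted Chi-Square is a legitimate primary test. It does not inflate false positives, the sample size was computed for it, and its power stays at the planned 80% in every scenario apart from simulation error. Preferring CMH is then a choice about efficiency. All of that stands. A reader might infer from the mismatch that the trial is underpowered or its result unreliable; the figures above show neither.

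The size also rests on undocumented inputs. The article gives neither the neoadjuvant share nor morbidity by stratum, and a gain near 4.5 points needs a stratum odds ratio above 5. This stands, so the size can only be given as a range that starts at zero.

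The different length of prehabilitation in the two strata (four weeks, or the whole of neoadjuvant treatment) might be read as evidence that the strata differ in morbidity. It applies only to the intervention arm. It may suggest a different treatment effect, but says nothing about control-arm morbidity.

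A reader might also infer that the design is stratified by centre. Section 2.9.1 does not name centre, and section 2.9.2 describes only how envelopes are divided and delivered. The variance argument is therefore not shown for centre, and randomisation already allows for chance imbalance between centres.

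Finally, a statistical analysis plan not shown may add adjusted analyses. That does not remove the point, because the article itself names the primary test, and the test named leaves out the factor used to randomise.

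**Conclusion.** The point holds as a matter of alignment and efficiency, not of validity. The stated primary test ignores the one stratification factor. It remains valid and keeps the planned 80% power. If morbidity differs by stratum, it is conservative: type I error at 116 patients is about 4.7% at 40%/60%, 4.1% at 35%/65% and 3.3% at 30%/70%. The power forgone against a stratified test is about 0 to 1 point for modest differences, about 3 points at 35%/65% and about 4.5 points at 30%/70%.

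These sizes assume equal strata, a common odds ratio and overall rates of 50% and 25%. If the strata do not differ, essentially nothing is lost. Section 2.11 specifies no confidence interval, so the excess width would concern an unadjusted interval only if one were reported.

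**What to change.** In section 2.11, replace the primary test with a Cochran-Mantel-Haenszel test stratified by neoadjuvant treatment (yes/no). Report the stratified risk difference with its 95% confidence interval, and keep the plain Chi-Square as a sensitivity analysis. Adjustment for centre may be added but is optional; if wanted, it should be stated in advance.

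The cost is one sentence of wording before database lock. The factor is known at randomisation, so no new data are needed, and the sample size can stay as it is. If the strata turn out alike, the stratified test performs practically the same as the plain one. Naming it now also settles which result is primary.

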## Introduction

1

Surgery is the main and only curative treatment option for gastric cancer (GC).^[1]^ Despite the progress in surgical and anesthetic techniques, gastrectomy remains associated with high postoperative morbidity (∼50%) and mortality (∼5%) rates.^[2–4]^ Furthermore, patients suffering postoperative complications are less likely to receive adjuvant therapy or must delay the initiation of it^[5,6]^ and it impairs the long-term outcomes.^[7]^ Therefore, there is a great need for novel strategies to reduce the postoperative morbidity after gastrectomy for GC.

Poor physical condition (determined by cardiopulmonary exercise testing), sarcopenia, and preoperative malnutrition often accompanies GC and represents decreased physiological reserve, predicting postoperative complications.^[4,8,9]^ Moreover, the majority of patients with resectable GC are considered for perioperative chemotherapy which improves oncological outcomes but impairs patients’ physical fitness before the surgery.^[10,11]^ Some patients’ risk factors are modifiable and may be improved within several weeks before surgery by a short multimodal prehabilitation consisting of physical training, nutritional adjustments and psychological support.^[12–14]^ Besides improved physical and nutritional status attributed to prehabilitation, a recent randomized control trial (RCT) showed a 51% reduction of postoperative complications after major abdominal surgery.^[15]^ Given the high morbidity rate, poor initial physical and nutritional status and the need for preoperative chemotherapy, GC patients would be ideal candidates to receive prehabilitation. To date, several studies already investigated the role of prehabilitation in esophagogastric surgery.^[16]^ However, most of these focused on patients receiving esophagectomy, with limited data for gastrectomy.^[16]^ A match pair analysis study showed reduced postoperative morbidity following prehabilitation in patients with GC and metabolic syndrome,^[17]^ while a small pilot study found increased physical status in elderly sarcopenic GC patients.^[18]^ However, these studies were rather small and inconclusive. There is a need for an RCT to address the role of prehabilitation in GC surgery.

The aim of this study is to demonstrate reduced postoperative morbidity after gastrectomy for GC in patients who undergo home-based prehabilitation.

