### Eligibility criteria

2.2

The study will include gastric cancer patients scheduled for elective total or subtotal gastrectomy at multidisciplinary team meetings. Patients scheduled for gastrectomy first and gastrectomy after neoadjuvant chemotherapy are eligible. Participants will be included after screening for eligibility and obtaining written informed consent. To participate in the study candidates must meet the following inclusion criteria:

1.Age ≥ 18 years.2.Patient agrees to participate in a clinical study.3.Patient requires surgical treatment for gastric cancer.

Patients will be excluded if they meet the following criteria:

1.Patient requires surgical treatment for gastric cancer recurrence.2.Patient condition not allowing to postpone surgery for at least 4 weeks.3.Patients’ physical or mental condition that does not allow the patient to participate in the prehabilitation program.

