#### Secondary endpoints

2.5.2

The secondary endpoints include:

1)Postoperative intrahospital and 90-day mortality rate2)Postoperative intrahospital and 30-day morbidity rate3)Physical status of the patient at baseline, pre-surgery, at discharge and 12 months after surgery by:Six-minute walk testSpiroergometry (VO_2,_ VO_2max_, AT)Grip strength testSit to stand testTimed up and go testThoracic excursion testInternational Physical Activity Questionnaire (IPAQ) score.4)Nutritional status at baseline, pre-surgery, 3, 6 and 12 months after surgery by:Blood albumin levelBioimpedanceNutritional Risk Score-2002 questionnaire score (NRS2002)5)Quality of Life at baseline, pre-surgery, 3, 6, and 12 months after surgery by:EORTC QLQ-C30 and STO-22 questionnaires scores6)Anxiety and depression level at baseline, pre-surgery, 3, 6 and 12 months after surgery by:Hospital anxiety and depression scale (HADS) score7)The proportion of patients completing the oncological treatment fixed in a multidisciplinary tumor board (including preoperative chemotherapy, surgery, and postoperative chemotherapy) at 12 months after treatment initiation

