## Discussion

3

Surgical resection remains the cornerstone of treatment with curative intent for GC. However, postoperative complications after gastrectomy are a significant problem resulting in increased treatment costs, prolonged hospital stay, delayed adjuvant therapy and impaired long-term outcomes.^[19–22]^ The physical, nutritional and emotional capacity of the individual patients predicts the postoperative outcomes.^[23–26]^ Some of the interventions, such as intensive intraoperative monitoring, well-timed admission to intensive care unit and enhanced recovery through ERAS protocols are proposed in the early perioperative period to improve the postoperative outcomes.^[27]^ Although, the ideal timeframe for prehabilitation intervention is the preoperative period, as the decline in physical and emotional status is to be expected after major surgery. An intensive postoperative program would be more detrimental to patient recovery and would fail to better prepare patients for surgery. It is rational to expect, that increasing patients’ physiological fitness before surgical trauma will preserve a higher level of functional capacity over the entire perioperative period and would hopefully extend postoperatively. The process of improving patients’ physical, nutritional, and emotional capacity before surgery has been termed multimodal prehabilitation. The goal centers on wholesome preparation of the patient to withstand the physical and emotional stress of surgery.^[28]^*Promising results of prehabilitation have been reported including reduced* postoperative complication rates^[15]^ and earlier recovery of physical function after major abdominal surgery.^[29]^ Although the current evidence from randomized studies remains weak and inconsistent, it suggests a potential strategy to reduce postoperative mortality rates.^[30,31]^ Only a few studies focused on prehabilitation for gastrectomy and none of them investigated the real multimodal prehabilitation approach in a randomized control trial.^[16,17]^ The matched-pair analysis by Cho et al^[17]^ showed the benefit of isolated exercise intervention for GC patients with a high body mass index (>25 kg/m^2^) and metabolic syndrome, while the pilot study by Yamamoto et al^[18]^ demonstrated the potency of exercise and nutritional intervention for sarcopenic and elderly GC patients. Despite this promising potential to improve postoperative outcomes by prehabilitation, the evidence level is low and further investigation is necessary. Currently, multimodal prehabilitation including exercise, nutritional and psychological interventions is under investigation in the ongoing PREHAB study.^[32]^ However, this study employs supervised exercise interventions, which require repeated clinical appointments. It becomes a geographical challenge when the cancer centers cover a large area with a widely spread population. The need for routine visits limits patients’ recruitment and adherence. To overcome such logistic issues, home-based prehabilitation was considered as an alternative, especially as recent data support the effectiveness of such programs for patients with lung and pancreatic cancer.^[33,34]^ Thus, our study was designed to investigate the trimodal prehabilitation in a home-based setting to limit participant visits, improve recruitment and reduce participant burden. Naturally, the compliance to the prehabilitation program in a home-based setting may be challenging. Therefore, the first three exercise trainings are supervised by a physiotherapist to ensure appropriate techniques and provide detailed written instructions for further personalized training at home. To assure compliance to the program we will use a self-reported diary and will implement a weekly phone call to assess patient adherence. The PREFOG study presented here will demonstrate whether home-based personalized prehabilitation will decrease the postoperative morbidity after gastrectomy for gastric cancer. Moreover, this study will allow us to determine whether prehabilitation can improve physical fitness and activity levels, nutritional status and quality of life, as well as reduce anxiety and depression levels after gastrectomy for gastric cancer.

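### The primary Chi-Square test is valid but leaves prognostic baseline data unused; prespecified adjustment would add roughly 0.5 to 6 points of power, depending on covariate strength

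*Protocol article*

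**What the plan says.** Section 2.11 (Statistical analysis) fixes the primary test: "The primary outcome analysis will be based on a Chi-Square test". No covariate or stratum enters it. The section ends with an open clause, "Other statistical methods will be used if there will be a need", which names no model and no covariates.

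Elsewhere the protocol treats baseline status as prognostic. The Introduction says that poor fitness, sarcopenia and malnutrition go with a state that "represents decreased physiological reserve, predicting postoperative complications". The Discussion says: "The physical, nutritional and emotional capacity of the individual patients predicts the postoperative outcomes".

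The data are largely collected already. Section 2.5.2 lists "Nutritional status at baseline, pre-surgery, 3, 6 and 12 months after surgery", with blood albumin among the measures, and also baseline physical tests. Section 2.5.3 records age. Section 2.9.1 makes neoadjuvant treatment the randomisation stratum. Section 2.2 describes patients as "scheduled for elective total or subtotal gastrectomy at multidisciplinary team meetings".

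Section 2.9.2 places the baseline assessment after the envelope has been opened and the patient told the result.

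**The concern.** If baseline status predicts complications as the protocol says, an analysis that conditions on it estimates the arm effect with less residual variation and has more power at the same sample size. A crude two-by-two comparison forgoes that gain.

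It matters because there is little reserve. If drop-out reaches the 10% allowed for, the trial has about 80% power, and only for a halving of the complication rate. Randomisation balances neoadjuvant treatment but not age or nutrition.

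The choice also has to be made in advance. In an open-label trial, an adjusted model brought in later under the open clause of 2.11 would be hard to defend as prespecified.

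**Working it through.** **Inputs.** From section 2.10: "the percentage of patients developing postoperative complications after gastrectomy is approximately 50% for the control group"; this "can be reduced to 25% in the prehabilitation group"; 58 per group, 80% power, two-sided 5%, 64 per group enrolled. Assumed: R², the share of outcome variance explained by the baseline covariates. The documents give no value, so a range is shown.

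**1. Reproduce the plan's figure.** The mean rate is 0.375.

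n = [1.96·√(2·0.375·0.625) + 0.8416·√(0.25 + 0.1875)]² / 0.25² = 57.67, so 58 per group. This agrees with the protocol. Then 58 × 1.1 = 63.8, so 64 per group.

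**2. Power of the unadjusted test at 58 per group.**
- SE under the null: √(2·0.375·0.625/58) = 0.0899
- SE under the alternative: √(0.4375/58) = 0.0869
- Power = Φ[(0.25 − 1.96·0.0899)/0.0869] = Φ(0.85) = 80.2%

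**3. Power with adjustment.** Multiply both standard errors by √(1 − R²). For R² = 10% the factor is 0.9487, and Φ[(0.25 − 0.1672)/0.0824] = Φ(1.005) = 84.3%.

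| Assumed R² | Power, 58 per arm | Gain (points) | Power, 64 per arm |
|---|---|---|---|
| 0% | 80.2% | 0 | 84.0% |
| 2% | 81.0% | +0.8 | 84.7% |
| 5% | 82.2% | +2.0 | 85.8% |
| 10% | 84.3% | +4.1 | 87.7% |
| 15% | 86.3% | +6.1 | 89.5% |

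In patients, 58 × (1 − R²) gives 56, 53 and 50 per arm at R² of 5%, 10% and 15%. That is worth about 4, 10 and 16 of the 116.

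**4. Check by simulation at 58 per arm, 50% versus 25%.** Gain of the adjusted logistic test of arm over the Chi-Square:
- One covariate (6000 trials per setting, Wald to likelihood-ratio test): about +2 to +3 points at R² 5%, +4 to +5 at 9%, +5 to +6 at 14%.
- Four covariates: +1 to +2, +3 to +4 and +4 to +5.
- Two continuous and one binary covariate (5000 trials): 80.7% to 81.3% at R² 3%, 80.1% to 82.6% at 8%, 79.6% to 83.6% at 11%.
- Three normal covariates (8000 trials): +0.5 points at a joint AUC of 0.56, +0.9 at 0.60, +2.8 at 0.66, +6.2 at 0.74.
- No prognostic value: about zero (for example 79.3% to 79.1%).

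Type I error of the adjusted logistic tests was 4.6% to 5.9% across these settings.

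**5. Sensitivity to the test used.** A linear-model risk difference with a conservative robust standard error (HC3) gained less. With one covariate the gains were +1.8, +3.4 and +4.5 points at R² 5%, 9% and 14%. With four they were −0.7, +1.3 and +2.7, and −2.5 with no prognostic value (type I error 3.9% to 4.8%). The p-value of the standardised risk difference was not itself simulated.

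**6. Room for covariates.** Expected events: 58·0.50 + 58·0.25 = 43.5, about 44. That supports a short list only.

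**The case against.** **The Chi-Square is not wrong.** It controls type I error and is the test behind the sample size. This stands. A reader might infer that the primary analysis is invalid, or that chance imbalance biases it. The documents do not support that: the error rate of an unadjusted randomised comparison already allows for chance imbalance.

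**The gain cannot be derived from the documents.** This also stands. A reader might infer a definite loss of several points. No section says how strongly any baseline variable predicts 90-day complications, and with weak covariates the gain is near zero.

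**80% is the floor of the plan.** Section 2.10 enrols 64 per group and allows for drop-out up to 10%. With no drop-out, power is 84.0% unadjusted. The formula then gives +2 to +5 points for R² of 5% to 15%. A simulation with three covariates gave −0.5 points at AUC 0.60, +1.0 at 0.66 and +4.0 at 0.74, partly because the Chi-Square is discrete.

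**The strongest named predictors are the least usable.** The protocol names fitness, sarcopenia, malnutrition and emotional capacity. Effort-dependent tests and questionnaires are taken after allocation is known, so knowledge of the arm could affect them. Of the covariates proposed here, only albumin stands for a predictor the protocol names. The lower part of the range may therefore be the realistic one.

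**Planned extent of gastrectomy may not be recorded.** Section 2.2 says it is scheduled at the team meeting. Section 2.5.3 lists type of surgery only among surgical details, which reads as the operation performed. A reader might infer that planned extent is available as a baseline covariate; the article does not show it.

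**Adjustment belongs in an analysis plan.** A plan not shown may add adjusted analyses. But the article does not leave the primary test open; it names one.

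**Conclusion.** The concern holds as a recommendation to improve efficiency. The primary test is valid but uses none of the baseline information that the protocol itself calls prognostic and, for age and albumin, already collects.

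Prespecified adjustment would add roughly 0.5 to 6 points of power at 58 evaluable patients per arm. This rests on the protocol's 50% and 25% rates, on an assumed R² of up to about 15% (or joint AUC of about 0.56 to 0.74), and on a logistic test with few covariates. With non-prognostic covariates the gain is about zero. With a conservative variance estimator and several covariates it can be slightly negative.

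The change is worth making because it needs little and type I error stays near 5%. It does not come entirely free: it requires an early commitment and a short covariate list.

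**What to change.** In section 2.11:
- Make the primary analysis a logistic regression of 90-day complication (yes/no) on arm, adjusted for the neoadjuvant randomisation stratum, age and baseline blood albumin, the last two kept continuous.
- Report the standardised (marginal) risk difference with its 95% CI, and take the p-value from that same estimate so that test and interval cannot disagree. Name the variance estimator.
- Keep the Chi-Square as a sensitivity analysis.
- Add planned extent of gastrectomy only if it is recorded before the envelope is opened. Do not adjust for the operation performed, which is a post-randomisation variable.
- Do not use effort-dependent or questionnaire baselines while baseline is assessed after allocation is disclosed (section 2.9.2).
- State how a missing albumin value is filled, for example by the overall mean, so that no randomised patient is lost from the model.

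Cost: one paragraph and a little analysis work, with no new patients. One new case report form field is needed only if planned extent is to be used. The covariates must be fixed before any outcome data are seen, and with about 44 expected events the list should not grow.

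### For continuous secondary endpoints measured at baseline and at three or four later visits, section 2.11 names only unadjusted two-group tests; a baseline- and stratum-adjusted model should be named instead

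*Protocol article*

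**What the plan says.** Section 2.5.2 of the protocol article sets a longitudinal schedule for four groups of secondary endpoints:

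- "Physical status of the patient at baseline, pre-surgery, at discharge and 12 months after surgery by" six performance or capacity tests and the IPAQ: baseline and three later visits.
- "Nutritional status at baseline, pre-surgery, 3, 6 and 12 months after surgery by" albumin, bioimpedance and NRS2002: baseline and four later visits.
- "Quality of Life at baseline, pre-surgery, 3, 6, and 12 months after surgery by" two EORTC questionnaires: baseline and four later visits.
- "Anxiety and depression level at baseline, pre-surgery, 3, 6 and 12 months after surgery by" HADS: baseline and four later visits.

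Section 2.11 gives the method for all secondary endpoints in one sentence, "For secondary endpoint analysis, Chi-Square or Fisher Exact test, T-Test or Mann-Whitney test will be used where appropriate", and adds: "Other statistical methods will be used if there will be a need". It does not say whether the tests apply to follow-up values or to changes from baseline, or at which visits.

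Two other sections bear on the point. Section 2.9.1 stratifies randomisation by neoadjuvant treatment. Section 2.9.2 fixes when baseline is taken: "After opening, the randomization information will be given to the patient, the baseline condition of the patient will be assessed".

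**The concern.** A T-Test or Mann-Whitney test compares two independent groups on one number per patient. It does not adjust for baseline or for the randomisation stratum, and it does not use the other visits. The trial collects all of this, so the named methods leave available precision unused.

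This matters because the Abstract and Discussion say the study will determine whether prehabilitation improves fitness, nutritional status and quality of life and lowers anxiety and depression. The sample size was set for the binary primary endpoint alone, and no power or precision is given for these secondary endpoints. The stratum is also likely to be prognostic here: the Introduction says preoperative chemotherapy impairs fitness before surgery, and section 2.3.2 makes the length of prehabilitation depend on the treatment pathway.

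**Working it through.** **The plan's own figure.** Section 2.10 gives 58 per group for 50% versus 25%, two-sided 5%, 80% power. The pooled-variance formula without continuity correction returns 58 (power 80.2%), and 58 × 1.1 = 63.8, so 64 per group and 128 in total. The figure reproduces. It concerns the primary endpoint only; its one use here is to supply a group size of 58.

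**Inputs for the secondary endpoints.**
- n = 58 per group (section 2.10). Fewer may remain at 12 months.
- Two-sided α = 0.05 (stated in section 2.10 for the primary endpoint).
- r, the correlation between baseline and follow-up: not in the document; assumed 0.3 to 0.8.
- Equal SD at baseline and follow-up, and a common linear relation in both arms: assumed.

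**Variance of the arm difference, relative to a test on follow-up values alone.**
- Follow-up values alone: 1
- Change from baseline: 2(1 − r)
- Baseline-adjusted (ANCOVA): 1 − r²
- ANCOVA relative to change score: (1 − r²) / [2(1 − r)] = (1 + r)/2

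**Detectable difference at 80% power.** For follow-up values alone this is √(2/58) × (1.960 + 0.842) = 0.52 SD. For the other two, multiply by the square root of the variance factor.

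| r | Variance, change score | Variance, ANCOVA | ANCOVA ÷ change score | Detectable, follow-up alone | Detectable, change score | Detectable, ANCOVA |
|---|---|---|---|---|---|---|
| 0.3 | 1.40 | 0.91 | 0.65 | 0.52 | 0.62 | 0.50 |
| 0.5 | 1.00 | 0.75 | 0.75 | 0.52 | 0.52 | 0.45 |
| 0.6 | 0.80 | 0.64 | 0.80 | 0.52 | 0.47 | 0.42 |
| 0.7 | 0.60 | 0.51 | 0.85 | 0.52 | 0.40 | 0.37 |
| 0.8 | 0.40 | 0.36 | 0.90 | 0.52 | 0.33 | 0.31 |

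**Power for an assumed true difference of 0.4 SD** (normal approximation).
- Unadjusted: 0.4 × √(58/2) = 2.154, and Φ(2.154 − 1.960) = 57.7%.
- Adjusted, dividing 2.154 by √(1 − r²): about 62% at r = 0.3, 70.1% at 0.5, 76.8% at 0.6, 85.5% at 0.7.

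For an assumed 0.5 SD the unadjusted test already has 76.8% power; adjustment gives 80.6%, 87.5%, 92.0% and 96.5% at the same four values of r.

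**What a post-disclosure baseline does.** The adjusted difference is (follow-up difference) − β × (baseline difference), with β = r when the SDs are equal. If knowing the allocation shifts one arm's baseline by s, the ANCOVA estimate moves by about r·s and the change-score estimate by the full s, while a comparison of follow-up values does not move. So the order of assessment in section 2.9.2 matters for any analysis that uses baseline.

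**The case against.** A reader might infer that the plan runs a separate test on raw values at every visit and discards baseline. The text does not say so. A T-Test on change from baseline fits the wording, and at r = 0.7 it recovers most of the gain (variance factor 0.60 against 0.51). At r = 0.5 it recovers none, and at r = 0.3 it is worse than follow-up values alone. ANCOVA is at least as precise as either throughout.

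A reader might also infer that much of the precision is lost. That depends on r. For patients on neoadjuvant treatment, baseline precedes the chemotherapy course as well as gastrectomy, and follow-up runs to 12 months. Low correlations are therefore plausible, and at r = 0.3 the gain is only 9% of variance.

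It is likewise tempting to count tests or to allege dropout bias. The article does not commit to testing every score at every visit, and it states no missing-data rule. Multiplicity and missing-data handling for secondary endpoints are commonly left to a full analysis plan, which is not shown, so neither is part of this finding.

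Finally, section 2.11 leaves room for other methods. That clause names no endpoint, trigger or model, so it cannot count as planned adjustment, although it does mean the two-group tests are not fixed as the only analysis. What stands is that the methods actually named for these endpoints are unadjusted two-group tests.

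**Conclusion.** The point holds as a matter of efficiency in secondary endpoints. Against a test on follow-up values alone, baseline adjustment removes 9%, 25% or 49% of the variance at r = 0.3, 0.5 or 0.7. Against a change-score test, ANCOVA has 0.75 to 0.85 of the variance at r = 0.5 to 0.7. These sizes rest on assumed correlations and equal SDs; the power figures rest also on assumed effects of 0.4 or 0.5 SD and 58 patients per group. The direction does not depend on those choices as long as r is above 0 (and, against change scores, below 1). The document does not support saying that the named tests are invalid or that baseline is certain to be ignored. The change should be made, but nothing in the primary Chi-Square analysis or the sample size depends on it.

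**What to change.** In section 2.11, replace the T-Test/Mann-Whitney wording for continuous secondary endpoints measured at baseline and later. Name either baseline-adjusted ANCOVA or a mixed model for repeated measures with arm, visit, arm-by-visit, baseline value, baseline-by-visit and neoadjuvant stratum. Report the adjusted difference between arms with its 95% CI. For clearly skewed scores, use a rank-based version of the adjusted analysis. A mixed model also uses patients with some visits missing, but it assumes the data are missing at random and does not settle how scores after death are treated; the text should not claim more for it.

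In section 2.9.2, move the baseline assessment ahead of opening the envelope for patients still to be enrolled. Section 2.8 says recruitment began in February 2020, so some baselines may already have been taken after disclosure. Acknowledge this as a limitation for the effort-dependent and self-reported measures.

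The cost is modest programming and a small change in the order of visit procedures. No new data are needed.
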